## Abstract

Liver cirrhosis is the 6th leading cause of death in adults aged 15–59 years in high-income countries. For many who progress to cirrhosis, the only prospect for survival is liver transplantation. While there is some indication that mesenchymal stem cells may be useful in reversing established liver fibrosis, there are limitations to their widespread use – namely their rarity, the need for extensive serial passaging and the associated potential for genomic instability and cellular senescence. To this end, we propose the use of allogeneic amnion epithelial cells. This clinical trial will assess the safety of intravenously delivered allogeneic human amnion epithelial cells (hAECs) in patients with compensated liver cirrhosis. This will also provide clinical data that will inform phases 2 and 3 clinical trials with the ultimate goal of developing hAECs as a therapeutic option for patients with cirrhosis who are at significant risk of disease progression. We will recruit 12 patients with compensated cirrhosis, based on their hepatic venous pressure gradient, for a dose escalation study. Patients will be closely monitored in the first 24 h post-infusion, then via daily telephone interviews until clinical assessment on day 5. Long term follow up will include standard liver tests, transient elastography and hepatic ultrasound. Ethics approval was obtained from Monash Health for this trial 16052A, “A Pilot Study Evaluating the Safety of Intravenously Administered Human Amnion Epithelial Cells for the Treatment of Liver Fibrosis, A First in Adult Human Study.” The trial will be conducted in accordance to Monash Health Human Ethics guidelines. Outcomes from this study will be disseminated in the form of conference presentations and submission to a peer reviewed journal. This trial has been registered on the Australian and New Zealand Clinical Trials Registry ACTRN12616000437460.

## Introduction

The World Health Organization has identified cirrhosis as the 6th leading cause of death in adults aged 15–59 years in high-income countries and the 9th most common cause of death in that age group in low-income countries (Lopez et al., 2006). Liver fibrosis results from a complex wound healing activity that involves increased extracellular matrix (ECM) synthesis as well as replacement of apoptotic or necrotic hepatocytes. Cirrhosis results from persistent and unregulated hepatic wound healing in response to ongoing hepatocyte injury. While previously considered as a static and irreversible outcome of progressive fibrosis leading invariably to death, we now know that this process is dynamic and potentially reversible for many patients. Extensive clinical data shows that liver fibrosis can resolve following adequate treatment or resolution of the injury stimulus, such as long term viral suppression in hepatitis B patients (Marcellin et al., 2013).

For many patients who progress to cirrhosis, a lack of response to existing therapy or the absence of effective treatment means that their only prospect for survival is liver transplantation. As the demand for liver donors continues to increase, there is a clear need for alternatives to whole organ transplantation for these patients. The use of stem cells for liver fibrosis has been previously proposed, based on preclinical evidence that mesenchymal stem cells (MSCs) ameliorate liver fibrosis in experimental animal models of the disease (Tsai et al., 2009; Wang et al., 2012; Meier et al., 2015). The postulated mechanisms of action include polarization of macrophages to an anti-fibrotic phenotype, reversal of activated stellate cells to a quiescent state (Chen et al., 2017) and general mitigation of hepatic inflammation.

To date, there are 56 clinical trials registered on ClinicalTrials.gov assessing the safety and efficacy of MSCs in liver cirrhosis. These include primary biliary cirrhosis, as well as liver cirrhosis associated with alcoholic liver disease and viral hepatitis. The MSCs used in these trials include both autologous and allogeneic sources, from adipose tissue, bone marrow, umbilical cord, and menstrual blood. A Korean study has reported promising results in a phase II trial where hepatic arterial injection of autologous bone marrow derived MSCs were reported to improve liver fibrosis (Suk et al., 2016). While such an outcome is promising, there remain many more trials whose outcomes are yet to be reported and may inform the future utility of MSCs for liver cirrhosis. Additionally, there are limitations to using MSCs associated with their rarity and their need for extensive passaging. These include the potential for genomic instability (Wang et al., 2013) and cellular senescence (Schellenberg et al., 2011) seen with passaged MSCs and as such, we have ventured into alternatives such as human amnion epithelial cells (hAECs), which have similarly potent anti-inflammatory and anti-fibrotic properties (Manuelpillai et al., 2010, 2012; Murphy et al., 2010a, 2011; Hodges et al., 2012; Hodge et al., 2014; Tan et al., 2016). Specifically, hAECs appear to influence inflammation and fibrosis by interacting with a multitude of cell types including fibroblasts (Vosdoganes et al., 2012), neutrophils (Tan et al., 2016), and macrophages (Manuelpillai et al., 2012; Tan et al., 2014). These outcomes appear to be independent of significant cell engraftment, but are instead indicative of a paracrine effect, similar to what has been previously reported in MSCs. Considering the complex cellular interactions involved in hepatic wound healing, hAECs may provide a multi-targeted approach needed for effective collagen degradation and hepatocyte regeneration. hAECs are isolated from the placenta, a widely available and non-controversial source. These fetal stem cells do not elicit immune-mediated rejection by the host and have intrinsic immune modulating characteristics that can induce hepatic fibrosis regression and stimulate liver regeneration. A clinically compliant method of hAEC isolation was previously established with a view to developing cell-based therapy (Murphy et al., 2010b). The hAECs are being used in a phase 1b trial, in babies with established bronchopulmonary dysplasia. As of the preparation of this manuscript, five babies have received allogeneic hAECs with no safety concerns (ACTRN12614000174684).

The objective of this phase 1 trial is to primarily assess the safety of intravenously delivered allogeneic hAECs in patients with compensated liver cirrhosis. This open label study will also provide clinical data that will inform phases 2 and 3 clinical trials with the ultimate goal of developing hAECs as a therapeutic option for patients with cirrhosis who are at significant risk of disease progression. For patients who progress to decompensated cirrhosis, the only effective therapeutic option is whole organ replacement. Liver transplantation is an established life-saving treatment for patients with end-stage liver disease; however, success depends on donor graft availability and recipients require life-long immunosuppression. In contrast, hAEC based therapy has the potential to prevent progression of cirrhosis and thus the need for transplantation.

## Methods and Analysis

### Study Design

In this open label phase 1 study, the safety and tolerability of hAEC transplantation will be examined in 12 patients with compensated cirrhosis (**Figure 1**). They will be divided into four cohorts. Each cohort will include three patients treated sequentially (patient 1, then patient 2, then patient 3). Each patient will be observed for serious adverse events (SAEs) for 5 days post intravenous (IV) hAEC infusion before the next patient is enrolled. In Cohort 1, three patients will receive hAEC (0.5 × 10^6^/kg) as a single IV injection. If no SAE occur within 5 days of the last infusion in Cohort 1, a further three patients will be sequentially enrolled in Cohort 2 and receive a higher hAEC dose (1.0 × 10^6^/kg) as a single IV injection. If no SAE occur within 5 days of the last infusion in Cohort 2, a further three patients will be sequentially enrolled in Cohort 3 and receive the same hAEC dose as Cohort 2 (1.0 × 10^6^/kg) as a single IV injection at days 0 and 28. If no SAE occur within 5 days of the last infusion in Cohort 3, a further three patients will be sequentially enrolled in Cohort 4 and receive the same hAEC dose as Cohort 3 (1.0 × 10^6^/kg) as a single IV injection at days 0, 28, and 56 (**Table 1**).

**FIGURE 1 F1:**
[figure not shown]
Studydesign.

**Table 1 T1:** Indicative minimal timeline.

**Cohort**/patient number	**C1**/1, 2, 3 (One infusion/patient)	**C2**/4, 5, 6 (One infusion/patient)
Week of study	0–8	12–20
**Cohort**/patient number	**C3**/7, 8, 9 (Two infusions/patient)	**C4**/10, 11, 12 (Three infusions/patient)
Week of study	24–52	44–76

#### The Development of Clinically Significant Portal Hypertension

The natural history of fibrotic liver disease can be divided into stages that are relevant to survival and therefore to the development of therapeutic interventions. Some patients will have a cause for chronic liver injury that is amenable to therapy, for example, long-term antiviral therapy in chronic hepatitis B can control viral replication and therefore inhibit immune mediated liver injury, resulting in cirrhosis reversal. For patients with persistent liver injury for which no treatment is available or in whom treatment fails, fibrosis will progress. The onset of clinically significant portal venous hypertension is considered the ‘tipping point’ in this progression as patients who develop it are at risk of developing ascites, variceal hemorrhage, and porto-systemic shunting with hepatic encephalopathy – all events which define the progression from compensated to decompensated cirrhosis.

Measurement of the gradient between venous pressure in the hepatic vein and that in the portal vein [hepatic venous pressure gradient (HVPG)] is widely accepted as the most accurate way to define the severity of portal hypertension and thus the risk of developing death. An HVPG ≥ 10 defines clinically significant portal hypertension. Annual mortality rates increase from 1% in patients with compensated cirrhosis (HVPG 6–10 mmHg) to 3% in compensated cirrhosis with an HVPG ≥ 10 but ≤ 12 mmHg to 10–30% in decompensated cirrhosis (HVPG > 12 but ≤ 16 mmHg) or >60% in patients with very high portal pressures (>16 mmHg). Therefore portal pressure reduction is a therapeutic goal since a decrease in HVPG of ≥20% from baseline or to ≤12 mmHg reduces the risk of variceal bleeding and other complications of portal hypertension such as ascites (D’Amico et al., 2006).

#### Direct Measurement of Portal Pressure

The difference between free hepatic venous pressure (FHVP) (or inferior vena cava pressure) and wedged hepatic venous pressure (WHVP) defines HVPG. To measure the WHVP, the hepatic vein is catheterized using a balloon-tipped catheter under fluoroscopic control. The balloon is inflated to completely occlude a branch of the hepatic vein and the pressure (WHVP) is recorded. At that moment, the pressure measurement represents the hepatic sinusoidal pressure.

Hepatic venous pressure gradient measurement does require an experienced operator, often an interventional radiologist, and is an invasive procedure. However, the risks associated with the procedure are generally minor complications such as transient cardiac arrhythmias, local pain at puncture site, or vagal reaction and occur infrequently (<1% of patients) (Suk, 2014). One major laboratory reported no fatalities in over 12,000 studies (Bosch et al., 2009).

## Non-Invasive Methods to Measure Liver Fibrosis and Portal Hypertension

### Transient Elastography

Liver stiffness measurement (LSM) by vibration-controlled transient elastography (TE) is now in common clinical use and has supplanted liver biopsy as a method for routine assessment of liver fibrosis. At Monash Health, Fibroscan^TM^ (Echosens, Paris) is used for this purpose. TE involves transmitting a low amplitude vibration at low frequency to induce an elastic shear wave in the liver. The wave propagation speed is captured using pulse-echo ultrasonic acquisition and directly relates to tissue stiffness. This technology has been validated in patients with chronic viral hepatitis (HBV, HCV), non-alcoholic fatty liver disease and alcoholic liver disease with good correlation with histological liver fibrosis. TE is used most often to determine whether or not a patient has cirrhosis and overall has a high negative predictive value meaning that it is useful in excluding cirrhosis. Accurate detection of cirrhosis is greatest in patients with a pre-test probability of cirrhosis >75% and may vary depending on the etiology of cirrhosis. In regard to detecting portal hypertension, a recent study evaluated the use of Fibroscan in addition to HVPG, hepatic ultrasound appearance and platelet count to detect clinically significant portal hypertension and shown in a single center study that this may be possible (Augustin et al., 2014) however, LSM cannot currently replace direct techniques such as HVPG.

## Identification and Recruitment of Study Participants

Potential study participants will be identified and recruited from liver clinics staffed by the Monash Health Gastroenterology and Hepatology Unit. Schedule of events are summarized in **Table 2**.

**Table 2 T2:** Schedule of events.

	Screening	Cell infusion				Follow up	
			
Cohort	All cohorts	1	2	3	4	All cohorts	
			
		Day 1	Day 1	Days 1, 30	Days 1, 30, 60	Day 5 post each infusion	Week 8 post last infusion
Informed consent	x						
Clinical assessment	x	x	x	x	x	x	x
Blood tests	x	x	x	x	x	x	
Serum sample	x	x	x	x	x	x	x
Chest X-ray	x						
HVPG	x						x
Ultrasound	x					x	x
Fibroscan	x					x	x
Biomarkers	x					x	x
Con meds	x	x	x	x	x	x	
hAEC infusion		x	x	x	x		

*Infusion days: observe in clinical trials unit for 24 h post infusion.*

## Inclusion Criteria

• Female or male• Age ≥ 18 years, ≤ 70 years

Aetiology of liver disease, one or more of:

• Non-alcoholic fatty liver disease• Alcohol related liver disease – abstinent for at least 3 months• Hepatitis C virus infection (treated or not treated)• Hepatitis B virus infection (on nucleoside analogs with normal ALT and HBV DNA) or inactive phase• HIV co-infection with HCV/HBV with virological suppression > 12 months• Cryptogenic cirrhosis• Hemochromatosis

Cirrhosis, defined as one of:

• Liver biopsy confirming histological features of cirrhosis• Transient elastography (Fibroscan) > 14.8 kPa• FIB 4 > 3.25• Clinical and radiological features that in the opinion of the investigator are consistent with a diagnosis of cirrhosis• Compensated cirrhosis defined by HVPG 6–10 mmHg.

## Exclusion Criteria

• Current or previous episodes defining decompensated liver disease, including variceal hemorrhage, hepatic encephalopathy, ascites• Listed for liver transplantation• Active autoimmune disease (IgG > 2x ULN)• Renal insufficiency (eGFR < 70 mL/min/1.73 m^2^)• HIV infection (untreated or uncontrolled viraemia)• HBV DNA > 200 IU/mL• Fulminant hepatitis (acute severe hepatitis with encephalopathy)• Primary sclerosing cholangitis• Primary biliary cholangitis• Portal/hepatic vein thrombosis• Significant comorbidity (chronic heart failure, COAD, pulmonary hypertension, diabetes)• Fibrotic liver disease other than cirrhosis (nodular regenerative hyperplasia)• Inability or unwillingness to provide informed consent.

## Primary Endpoint

The primary objective of this pilot study is to establish the safety and tolerability profile of transplanted hAEC in adult patients with compensated cirrhosis.

## Secondary Objectives

The following secondary objectives will inform the development of future clinical trial protocols and enable appropriate statistical analysis

• Assess changes in baseline CPT, MELD, HVPG, liver stiffness and non-invasive tests at 3 and 6 months following cell exposure• Assess health related quality of life• Assess liver related clinical events.

## Design and Conduct of the Study

### hAEC Retrieval and Preparation

Healthy pregnant mothers delivering at term gestation will be approached and consented for donation of their amniotic membranes. The donor mothers will be screened for all viral and other infections (CMV, HIV, Hepatitis B and C virus – similar to blood transfusion donors) on day of delivery. These investigations will be repeated 3 months later again to exclude pathogens that might have been in incubation during delivery. hAECs will be isolated in a GMP-certified Biospherix Unit housed in the Monash Health Translation Precinct – Translational Research Facility (MHTP TRF) and stored in a secure and dedicated liquid nitrogen dewar until the donor has been cleared for use.

## Cell Harvest, Isolation, and Administration

### hAEC Isolation

Amniotic membranes will be collected from healthy women with a normal singleton pregnancy undergoing Cesarean section at term (37–40 weeks gestation). Informed written consent is obtained prior to surgery.

Human amnion epithelial cells are isolated from amnion membranes and purity is assessed as described previously (Murphy et al., 2014). Briefly, amniotic membranes are minced and digested twice for 60 min at 37°C using animal-product free recombinant trypsin (TrypZean, Sigma Aldrich) and re-suspended in animal-product free culture medium (EpiLife, Life Technologies) for cell counting. Purity is assessed by flow cytometry for EpCam+ cells (BD Biosciences) and batches that are >90% EpCam positive but negative for MSC markers (CD90, CD105) are cryopreserved in animal product free cryopreservation media (Cryostor CS5, Stem Cell Technologies).

## Monitoring

### Screening to Day of Treatment

Prior to first hAEC infusion, the following procedures will be performed:

• Obtain patient demographic information• Physical examination and vital signs• Baseline laboratory testing: full blood examination, liver function tests, INR, alpha fetoprotein, renal function tests, serum electrolytes, ESR, CRP, pregnancy testing in females• Serum sample (10 mL) for storage• Calculate CPT score and MELD score• Transient elastography• Performance status (ECOG)• Chest X-ray.

### Monitoring on Day of Treatment

• Patients will be observed and monitored in the TRF Clinical Centre with appropriate monitoring facilities. Facilities to treat anaphylaxis are present and experienced trial personnel will be in attendance.• Blood pressure and pulse oximetry monitoring every 15 min during the first 2 h, every 30 min for the next 2 h, every hour following that through to 24 h.• Temperature measurement q30 min for 4 h and then hourly for first 12 h.• Record any adverse events (as described below) and concomitant medications.• Serum sample (10 mL) at 12 and 24 h for storage.

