### Monitoring Days 2–5 Post hAEC Transplantation

The following will be performed after 24 h of therapy:

• Post infusion days 2–4: daily telephone contact to assess overall status• Post infusion day 5: clinical assessment including open ended questioning to ascertain any adverse events, recording concomitant medications and measuring FBE, UEC, LFT, AST, CRP, INR. A 10 ml serum sample will be obtained for storage.Post infusion week 8 for cohorts 1 and 2, week 12 for cohort 3, week 16 for cohort 4: Routine laboratory tests (as for day 5), Fibroscan and HVPG measurements will be performed and a serum sample (10 ml) obtained for storage.

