### Adverse Event Definition

An adverse event (AE) is any untoward medical occurrence in a patient administered a pharmaceutical product and that does not necessarily have a causal relationship with this treatment. An adverse event can therefore be any unfavorable and unintended sign (including an abnormal laboratory finding), symptom, or disease temporally associated with the use of a medicinal product, whether or not related to the medicinal product. Pre-existing conditions that worsen after drug administration will be reported as adverse events. Generally an increase/worsening of pre-existing disease status more than 30% of baseline is reported as an adverse event (for e.g., a baseline heart rate increase from 150/min to more than 195/min, an increase of FiO_2_ requirement from a baseline 50% to more than 65%).

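### Scheduled temperature stops 12 h before the end of the 24 h post-infusion stay (8 h on a less natural reading), while blood pressure and oximetry continue hourly to the end

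*Protocol article*

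**What the plan says.** The protocol article's section Monitoring on Day of Treatment gives two schedules for the same stay. Blood pressure and pulse oximetry are taken every 15 min for 2 h, every 30 min for the next 2 h, and then "every hour following that through to 24 h". The temperature line reads "Temperature measurement q30 min for 4 h and then hourly for first 12 h".

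The footnote to Table 2, under Identification and Recruitment of Study Participants, fixes the length of stay: "observe in clinical trials unit for 24 h post infusion".

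Other means of detection are also stated:
- The day-of-treatment section places the patient in a centre with monitoring facilities and experienced staff present, and tells them to "Record any adverse events (as described below) and concomitant medications".
- The same section has serum drawn at 12 h and 24 h, but for storage only.
- Monitoring Days 2–5 Post hAEC Transplantation provides "daily telephone contact to assess overall status" on days 2 to 4.
- On day 5 it provides "clinical assessment including open ended questioning to ascertain any adverse events, recording concomitant medications and measuring FBE, UEC, LFT, AST, CRP, INR".

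Escalation rests on serious adverse events: under Study Design, "Each patient will be observed for serious adverse events (SAEs) for 5 days post intravenous (IV) hAEC infusion".

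**The concern.** Safety and tolerability are the primary objective of this first study of the cells in adults. Under Outcomes, infection shown by clinical signs is one of the listed safety outcomes. Expected Outcomes accepts a theoretical risk of systemic effects like those of a blood transfusion. Neither section names fever, so the link from temperature to these outcomes is clinical inference. It is a reasonable one, since the protocol itself schedules repeated temperatures in the hours after infusion.

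The two schedules end at different times, and the article gives no reason. In the final part of the stay the patient is still in the unit and still has blood pressure and oximetry taken every hour, but fever is no longer sought by measurement. After discharge, contact is by telephone until day 5, so these are the last hours in which temperature can be taken without asking anything of the patient. At stake is a possible missing entry in the adverse-event record. The Adverse Event Definition is wide enough to take in any unfavorable sign, so a mild fever would count as an event if it were found.

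**Working it through.** The article states no figure on this point, so there is none to reproduce. The check is a count of scheduled post-infusion readings, excluding any taken at time zero.

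**Inputs**
- Blood pressure/oximetry and temperature intervals: Monitoring on Day of Treatment.
- Stay of 24 h after each infusion: Table 2 footnote.
- Four cohorts of three patients with 1, 1, 2 and 3 infusions per patient: Study Design.

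**Planned infusions**

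3×1 + 3×1 + 3×2 + 3×3 = 21, assuming all are given.

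**Blood pressure/oximetry sets per stay**

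8 (every 15 min for 2 h) + 4 (every 30 min for 2 h) + 20 (hourly, hours 5 to 24) = 32. Of these, 12 fall after hour 12 and 8 fall after hour 16.

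**Temperatures per stay**

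| | Plain reading: hourly up to hour 12 | Less natural reading: hourly for 12 h after the first 4 h |
|---|---|---|
| Scheduled now | 8 + 8 = 16 | 8 + 12 = 20 |
| Last reading | hour 12 | hour 16 |
| Gap before hour 24 | 12 h (12/24 = 50%) | 8 h (8/24 = 33%) |
| Blood pressure/oximetry sets in the gap | 12 | 8 |
| With hourly temperature to hour 24 | 8 + 20 = 28 | 28 |
| Added per stay | 28 − 16 = 12 | 28 − 20 = 8 |
| Added over 21 infusions | 12×21 = 252 | 8×21 = 168 |

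The gap exists on both readings.

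**What else could find a fever in the gap**
- Staff in attendance could take an unscheduled temperature after a complaint or an abnormal blood pressure or saturation. Nothing requires it.
- The record of concomitant medications would show an antipyretic, if one was given.
- The 24 h serum is stored, and no C-reactive protein or white cell count is named for that time.
- The day 2 to 4 calls could pick up a fever that the patient felt.
- The day 5 blood count and C-reactive protein could show an infection that persisted.

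None of these is a scheduled temperature in the gap, and none reliably finds a short fever with few symptoms.

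**Share of the 5-day window, taken as 120 h**

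On the plain reading, scheduled temperature covers 12/120 = 10% now and 24/120 = 20% with the change. The other 96/120 = 80% falls after the in-unit stay, where the article names no temperature.

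**The case against.** The strongest reply is that this is a deliberate schedule and that nothing in the article shows 12 h to be too short. Blood pressure and oximetry bear directly on named outcomes (hypotension, hypertension, hypoxaemia), whereas temperature is not named. Infection has its own route through clinical signs, C-reactive protein, white cell count and cultures, with bloods on day 5. The patient is in a staffed unit. The fever at issue would have to be brief, cause little complaint, arise only in the last hours of the stay and leave no trace by day 5. Such an event would not of itself be serious. The change also leaves 80% of the 5-day window without a scheduled temperature.

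Most of this stands, and it sets the weight of the point. It does not remove the gap: each safeguard needs someone to notice or report something, and the measurement that would replace noticing is cheap while the patient is being checked hourly anyway. The hours after discharge are a different matter, because a reading there would need a new procedure for the patient.

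A reader might infer more than the text supports:
- **That the protocol contradicts itself.** It does not. Two schedules of different length are stated openly.
- **That patients are unmonitored late in the stay.** They are not. Staff, hourly blood pressure and oximetry, and adverse-event recording all continue.
- **That a certain number of fevers will be missed.** The article gives no rate for late fever, so no number can be derived. The counts above are of readings and hours.
- **That dose escalation is unsafe.** The escalation rule depends on serious adverse events and is not touched by this line.

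**Conclusion.** The point holds as a minor gap in the measurement schedule. The final 12 h of each stay, or 8 h on the less natural reading, have no scheduled temperature, although blood pressure and oximetry are scheduled throughout. A symptomatic fever would probably prompt a check. A brief fever with few symptoms could go unrecorded. The consequence is confined to the completeness of adverse-event ascertainment for the primary safety outcome.

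This rests on three things: the schedule is followed as written, all 21 planned infusions are given, and fever is accepted, as clinical inference, as relevant to the infection and transfusion-like risks that the article describes. How often such a fever would occur is unknown.

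**What to change.** In Monitoring on Day of Treatment, change the temperature line to: every 30 min for 4 h, then hourly to 24 h, taken with each hourly blood pressure and oximetry set. This also removes the uncertainty over whether the present line ends at hour 12 or hour 16.

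The cost is 8 to 12 extra readings per stay (168 to 252 over 21 infusions), with no added visit and no longer stay. The article does not say whether the existing sets are manual or automated. If manual, no extra bedside contacts are needed. If automated, there could be up to one extra contact per added reading, so 0 to 12 per stay and 0 to 252 in all. The downside for the patient is slight additional disturbance overnight.
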